#### **Treatment Conditions.**

**Best Practices:** The 2008 Clinical Practice Guidelines for smoking cessation recommends that pregnant smokers be provided with the 5As. Briefly, these guidelines stipulate that practitioners should implement the following steps at obstetric visits: (1) Ask about smoking status at the first prenatal care visit; (2) Advise those who endorse smoking about the potential harms of smoking to mother and fetus and recommend quitting; (3) Assess the willingness of smokers to make a quit attempt during pregnancy; (4) Assist those willing to make a quit attempt by helping to establish a quit plan, referring them to the Vermont pregnancy-specific quit line and offering assistance with making the initial contact, and by providing them with a copy of the pregnancy-tailored self-help guide "Need Help Putting Out That Cigarette?", distributed by the American College of Obstetricians and Gynecologists; (5) Arrange for follow-up contacts on smoking at subsequent prenatal care visits. As there may be differences in the extent to which the 5As are implemented across obstetric clinics, research staff will implement the 5As at three assessments that take place during pregnancy (see Assessment Procedures below) to decrease between-subject variability in exposure to best practice guidelines. At the first antepartum assessment, staff will complete a fax referral form for participants to the Vermont (or other state) pregnancy-specific quit line, operated by Free & Clear, which provides 9 free telephone-counseling calls with a trained smoking-cessation coach during pregnancy (5 calls) and postpartum (after birth) (4 calls). All calls average approximately 10 minutes. The quit line attempts to reach women five times within a 3-day period for each scheduled phone counseling session. In addition to completing the 5As and referring women to the quit line, all women in the best practices condition will also receive the smoking cessation advice that is provided at their obstetric clinic. Note that pregnant women

seeking smoking cessation treatment in the community often do not receive cessation-focused follow-up visits after endorsing that they are current cigarette smokers, nor do providers or community health workers typically submit referrals for them to a quit line. As we take these extra steps, we refer to this condition as “best practices” rather than “usual care.”

**Best Practices + Financial Incentives:** Women assigned to this condition will receive the best practices treatment described above plus the remote incentives intervention. As mentioned previously, participants will set a quit date during their orientation session for either the first or second Monday following the session. They may practice submitting samples (for which staff will provide feedback) prior to their quit date if desired, however this is not required as they would have already provided an initial sample to validate their smoking status prior to being randomized. Once the quit date arrives, participants will submit two breath CO samples each day, separated by 8 hours from one another. A day will start at 5:00 a.m. and end at 4:00 a.m. (EST). The app will indicate to participants when samples can be collected because the “post video” button will be locked for 8 hours after the first sample of the day is submitted.

Beginning on the quit date and extending for one week, participants will be required to submit twice daily CO samples. All samples  $\leq 6$  ppm will be considered negative and those  $> 6$  ppm will be considered positive. Requiring frequent testing during week 1 only will permit participants the opportunity to earn frequent reinforcement while their salivary cotinine levels decrease more gradually if participants are not smoking over the course of week 1 of treatment. As with our prior and ongoing trials, the value of the incentive will increase with consecutive negative samples indicating smoking abstinence. If a sample has not been submitted within the specified 8-hour time window, an electronic prompt will be sent to submit a video two hours before the time window expires. Missed samples will be considered positive unless extenuating circumstances are reported (e.g., lost, stolen, broken phone). The schedule of potential earnings will be consistent with our prior trials adjusting for inflation. Thus rather than a maximum potential earnings of \$1,200 (2002 USD), participants in the proposed study may earn up to \$1,620 (2017 equivalent of \$1,200 in 2002) for sustaining smoking abstinence during pregnancy and for 12-weeks postpartum. The schedule of potential earnings will start at \$6.25 for the first negative sample and increase by \$1.00 for each consecutive negative sample. Thus the second negative sample will be worth \$7.25, the third worth \$8.25, and so on, until incentive values plateau at a maximum of \$33.25. If a participant submits a breath CO  $> 6$  ppm during week 1 or a positive saliva cotinine test any time after week 1, the value of the incentive will be reset to the initial value of \$6.25. This reset component is critical to protect against relapse once an initial period of abstinence has been achieved.

Following the initial quit week during which participants submit twice daily breath CO samples, the schedule of monitoring will be reduced and saliva cotinine will be used to determine smoking status. Only tests where the display indicates negative samples will result in subjects earning reinforcement. Specifically, during weeks two through six, participants will submit videos of themselves completing saliva cotinine tests twice per week, then once per week from week seven until delivery. During the once per week phase, the specific day on which participants are required to submit a sample will be determined quasi-randomly (at least two days apart). The sample will be prompted electronically via a text message at the start of the day and the participant will have up to eight hours to provide the sample. This provides a balance between a schedule that is sufficiently unpredictable that participants who are no longer abstinent may be detected, while at the same time providing them with a reasonable time frame to submit a sample upon being prompted to do so. The schedule of potential earnings during weeks two until delivery will be a continuation of the escalating pay schedule from the initial quit week. Importantly, intermittent reinforcement schedules induce more persistence than frequent, predictable schedules, thus the schedule we are proposing may be optimal for promoting persistence and sustained abstinence.

As women who quit smoking during pregnancy are particularly vulnerable to relapse during the early postpartum, the frequency of monitoring will increase to twice per week for the initial four weeks postpartum. After the first month, monitoring will be returned to the weekly, quasi-random prompted monitoring schedule for the next 8 weeks. The opportunity to earn incentives will be terminated at the end of postpartum week 12, consistent with our prior and ongoing trials thereby permitting us to compare the results of the proposed intervention to our group’s traditional, in person financial incentives interventions.

**Validating Videos.** Research staff will validate participant videos daily during the workweek. After logging in, the process takes less than ten minutes per video. To be considered valid, the videos of breath tests during week 1 must meet the following criteria: (a) have an authentic user (i.e., a known, enrolled participant), (b) participant can be seen holding her breath for the required duration, (d) participant can be seen and heard exhaling into the mouthpiece, and (e) participant displays CO reading at the end of the video until the monitor indicates that the reading is complete. In [name] recent controlled trial that required remote submission of breath CO samples, only 39 of 4,774 (0.8%) total samples submitted were problematic. Of these 39, 35 involved technical issues and four involved discrepancies between the user input and the video-confirmed CO reading. None of the discrepancies resulted in vouchers being provided erroneously. Regarding videos of saliva cotinine testing from week 2 through 12 weeks postpartum, videos must meet the following criteria: (a) have an authentic user (i.e., a known, enrolled participant), (b) saliva cotinine test kit is in view for entire duration of the video, (c)

CHSMS (Medical) #17-0604 Approved: 4/3/2020

participant permits ample time to collect the sample and collect a reading, and (d) test result is displayed clearly at the end of video.

**Delivering Incentives.** Participants' account activity box on their homepage will display their recent and cumulative earnings. In our group's previous studies that used similar schedules of potential earnings to what we are proposing here, participants earned (on average) \$550 during the intervention. Participants in the proposed study will receive a True Link or PEX Debit Card at the beginning of the intervention onto which incentive payments will be loaded contingent on their submission of breath CO samples indicating smoking abstinence. These debit cards do not require a credit history check, and Vermont residents with these cards pay no monthly fees or ATM withdrawal fees at non-MoneyPass ATMs. Moreover there are no costs for using the True Link or PEX Debit Cards for in-store or online shopping. Thus we anticipate that few participants will object to receiving and using these cards. Research staff will load money onto participants' study debit card after reviewing each video and determining that the video meets the criteria for validation above. Comparable methods of incentive delivery have been employed in computer-based financial incentives treatments targeting the general population of smokers. In these studies, participants redeemed their incentive earnings via online vendors (e.g., Amazon.com) or had their earnings transferred to a PayPal account after their breath CO submissions were validated. Providing participants with a debit card that is specifically and explicitly for study purposes eliminates the requirement on their part to open a PayPal account, which was unattractive to some participants perhaps because they were not comfortable providing their banking account information to open the PayPal account. Importantly, in-person financial incentives treatments typically require research staff to venture into the community to make a voucher purchase (e.g., gift card) in person and then deliver it to the participant. In contrast, the technology-based method that we are proposing is easy to implement and will decrease both staff travel time to redeem vouchers, as well as the immediacy between engaging in the target behavior and receiving reinforcement.

**For research involving survey, questionnaires, etc.:** Describe the setting and the mode of administering the instrument and the provisions for maintaining privacy and confidentiality. Include the duration, intervals of administration, and overall length of participation. (describe and attach all instruments)

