Participants randomized to the incentives condition will select a quit date (either the first or second Monday following their enrollment), and will submit videos of themselves blowing into a breath CO monitor twice daily during week 1. They will receive incentives for every sample where expired breath CO is  $\leq 6$  ppm. Beginning in week 2 and extending through week 6, participants will submit videos twice per week (Monday/Thursday) for which they will receive incentives for providing videos of themselves completing saliva cotinine tests indicating smoking abstinence. From week 7 until delivery, participants will submit videos once per week and will continue to receive incentives for saliva cotinine tests indicating no smoking. During the postpartum period, women will submit videos twice weekly for the first 4 weeks and once weekly from weeks 5-12. The first negative breath CO or salivary cotinine sample is worth \$6.25 and each consecutive negative sample will increase the value of the incentive by \$1.00 up to a maximum of \$33.25 per sample. Missed samples or samples that indicate smoking will be worth \$0 and will reset the incentive at its starting value. However two consecutive negative samples following the slip will restore the incentive to its value before the slip. The maximum earnings in this condition is \$1,620, which is the same as our prior studies adjusting for inflation. A proposed voucher schedule is attached.

Women in both conditions will complete seven formal assessments of their smoking status during their participation (intake, early pregnancy or 1 month after enrollment, late pregnancy or  $\geq 28$  weeks gestation, and at 4-, 8-, 12-, and 24-weeks postpartum) along with a treatment acceptability questionnaire and semi-structured interview on barriers and facilitators of treatment engagement. Women will receive \$50 for completing each of these (\$400 total)

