**METHODS AND PROCEDURES**

**Study Design:** Describe the research design, including a description of any new methodology and its advantage over existing methodologies.

We are proposing a two condition, parallel groups, randomized controlled trial (RCT) of a mobile-phone-based financial incentives intervention targeting economically disadvantaged pregnant cigarette smokers. The experimental group will receive electronic vouchers contingent on the remote submission of breath carbon monoxide (CO) samples indicating smoking abstinence whereas the control group will receive best practices for promoting smoking cessation. The use of a best practices control group reflects a real-world comparison condition in that all women will receive the treatment that practitioners in the community are instructed to provide (i.e., the 5As plus quit-line referral) thereby enhancing the ecological validity of the study, while also minimizing between-subject variability in the extent of participants' exposure to these practices by implementing these treatment components ourselves (described in greater detail below). Although one common alternative is to use a non-contingent incentives control group which equates both groups in terms of overall earnings, a meta-analysis conducted by our group showed that non-contingent incentives have no impact on abstinence levels above no-incentive control conditions. Alongside the two condition, parallel groups RCT described above, we will recruit an additional 60 American Indian/Alaska Native (AI/AN) women at another site (Alaska Native Tribal Health Consortium, Anchorage, Alaska) to examine effects of the present mobile-phone-based incentives intervention among this specific subgroup of women. Although this smaller subset of women will be randomized separately within an arm that is separate from the main trial, all study protocols and procedures will be identical in the AI/AN arm relative to the main trial. The rationale for a separate arm targeting AI/AN women is that smoking prevalence is substantially higher among this subpopulation (i.e., ~ 36% for AN women (Patten et al. 2018) versus ~ 13% among U.S. pregnant women overall (Kurti et al., 2017), they exhibit unique tobacco use characteristics including use of a homemade smokeless tobacco (Iqmik, Hurt et al., 2009), and very few smoking cessation interventions have been implemented specifically among AI/AN women (Patten et al., 2010; Patten et al., 2018). Thus, the present smartphone-based incentives intervention—which has never been implemented previously among this subpopulation—will be examined among a subset of 60 AI/AN women. AI/AN women will be recruited at a separate site (ANTHC, Anchorage, AK), and separate IRB approvals will be obtained as mandated by the collaborating location.

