**Participants** Study participants will be 152 pregnant Medicaid recipients  $\geq 18$  years of age and their infants (304 subjects total). Mom's will be recruited from obstetric practices and WIC offices located in all Vermont counties, and from obstetric practices and WIC offices outside Vermont. We will use the same procedures to recruit as our prior and ongoing trial, as well as the print and online advertising strategies (e.g., local newspapers, Facebook, Craigslist) that were developed for use in our current trial. An additional, smaller subset of 60 pregnant AI/AN women will be recruited using a combination of these two methods in Alaska. Briefly, pregnant women attending their first prenatal care visit will be identified from the obstetric clinic's appointment schedules. Receptionists at each practice will request that these women complete a brief self-administered smoking-screening form containing a multiple-choice question on smoking status that has been validated to enhance accurate reporting. These forms will be returned via fax to the Substance Abuse Treatment Center ([name]). Only those identified as key personnel on the proposed study have access to the fax machine in the SATC. Women who endorse smoking in the 7 days prior to completing the screening form and provide contact information will be contacted by research staff to further verify study eligibility and provide additional information about the study. Regarding our print and online advertising strategies, participants will self-refer after seeing our ads and will complete a screening online or over the telephone with research staff. Prior to enrolling in the study, women who self-refer will be asked to sign a medical release form allowing us to contact their healthcare provider or local WIC director to verify their current pregnancy status.

For inclusion in the study, women must meet the following criteria: (a)  $\geq 18$  years of age, (b) report being smokers at the time they learned of the current pregnancy, (c) report smoking in the 7 days prior to completing their preliminary eligibility screening, (c)  $\leq 25$  weeks pregnant, (d) speak English, (e) own a smartphone (Android or iOS; 81.8% of pregnant women in wave 1 [2013-2014] of the Population Assessment of Tobacco and Health

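### The only definition of the sampling day is in Eastern time; read with the identical-procedures rule, it puts Alaskan women's weekly eight-hour sampling window at about 1 to 9 a.m. local time

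*Protocol*

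**What the plan says.** The definition of a day stands in the protocol, Treatment Conditions, under Best Practices + Financial Incentives, in the text on twice-daily breath samples in week 1: "A day will start at 5:00 a.m. and end at 4:00 a.m. (EST". No other definition of a day appears, and there is no local-time rule for participants elsewhere.

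The same subsection later describes the once-weekly saliva phase, from week 7 to delivery, in which the sampling day is chosen quasi-randomly: "The sample will be prompted electronically via a text message at the start of the day and the participant will have up to eight hours". The stated aim is a balance between unpredictability and "providing them with a reasonable time frame to submit a sample upon being prompted to do so". The schedule recurs after birth: "After the first month, monitoring will be returned to the weekly, quasi-random prompted monitoring schedule for the next 8 weeks".

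Study Design adds 60 American Indian/Alaska Native women recruited in Anchorage and says that "all study protocols and procedures will be identical in the AI/AN arm relative to the main trial". Recruitment says the same of everything after the advertisement. Consent Procedures lists only the initial advertising and the separate randomization as differences. Main-trial women may also come "from obstetric practices and WIC offices outside Vermont".

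Under the Protocol Summary, a missed sample is worth $0 and "will reset the incentive at its starting value"; two consecutive negatives then restore the earlier value. The week-1 text counts a missed sample as positive unless extenuating circumstances are reported, and provides an electronic reminder two hours before the window closes.

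**The concern.** The intervention works by paying promptly for verified abstinence. If the prompt and its window follow Eastern time everywhere, an abstinent woman in Anchorage is prompted while she is probably asleep, on a day she cannot foresee, and has little of the window left when she wakes. A miss then costs her the payment and the escalated value although she has not smoked.

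At stake is what the Alaskan arm can show. Statistical Methods presents it as a first feasibility and proof-of-concept test, and Sample Size Justification says its results will inform power calculations for larger studies. Missed samples caused by the clock could be read there as poor engagement or a weak effect. The arm would also not have received the intervention on the same terms as the main trial, contrary to what Study Design says.

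**Working it through.** **Inputs from the protocol.** Day starts at 5:00 a.m. Eastern and ends at 4:00 a.m.; the weekly prompt comes at the start of the day; window 8 hours; incentive $6.25, rising by $1.00 per consecutive negative to $33.25.

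**Inputs assumed.** Alaska is four hours behind Eastern time and Pacific time three hours behind; the protocol gives no offsets. Waking at 7 a.m. and going to bed at 11 p.m. are illustrations.

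**Weekly window.** Local start = 5:00 minus the offset; local close = start + 8 hours.

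| Place | Opens | Closes | Hours left after waking at 7 a.m. |
|---|---|---|---|
| Vermont | 5 a.m. | 1 p.m. | 6 |
| Pacific zone | 2 a.m. | 10 a.m. | 3 |
| Anchorage | 1 a.m. | 9 a.m. | 2 |

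These hold when both places are on standard time or both on daylight time. If EST is taken literally all year, every local time is one hour later in summer: 2 to 10 a.m. in Anchorage and 6 a.m. to 2 p.m. in Vermont. The four-hour gap remains.

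**Reminder.** If the two-hour reminder also applies in the weekly phase, it reaches Anchorage at 9 − 2 = 7 a.m. (8 a.m. in the literal-EST summer case).

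**Week 1.** The Eastern day runs from 1 a.m. to midnight in Anchorage. The last first sample that still allows a second is 4:00 a.m. − 8 h = 8 p.m. Eastern, which is 4 p.m. in Alaska. A woman awake from 7 a.m. to 11 p.m. must in any case give her first sample by 11 − 8 = 3 p.m. in both places, so the Eastern clock does not bind in week 1.

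**Cost of one isolated miss at the plateau.** The restore rule does not say whether the second negative is itself paid at the restored value.
- If the two following negatives pay $6.25 and $7.25: 33.25 + (33.25 − 6.25) + (33.25 − 7.25) = 33.25 + 27.00 + 26.00 = $86.25.
- If the second is paid at the restored value: 33.25 + 27.00 = $60.25.

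**Phases affected.** Week 7 to delivery, and the eight weekly prompts in postpartum weeks 5 to 12. No start-of-day prompt with an eight-hour window is stated for weeks 2 to 6 or postpartum weeks 1 to 4.

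**The case against.** The strongest reply is that the Eastern-time sentence belongs to the week-1 breath samples. The weekly-phase text gives no clock time and does not refer back, and its stated aim of a reasonable response time would be defeated by a text at 1 a.m. So a reader might infer that the protocol itself schedules a 1 a.m. prompt for Alaska. It does not say so in one place; that follows only from joining three statements. This part of the objection stands. It does not remove the point, because nothing else defines a day, both phases run on the same app, and the identical-procedures statements leave no room for a local rule.

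Second, there is mitigation: the excusal clause, restoration after two negatives, and the reminder, which at 7 a.m. would leave two hours for a test of about five minutes. This softens the effect. But the examples of excusal concern a phone that is lost, stolen or damaged, not a prompt sent during sleep, and the reminder is stated only in the week-1 text.

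Third, the consequences are bounded. Assessment Procedures determines smoking status in both conditions from samples at formal assessments, not from these prompts. The Alaskan arm is randomized separately and no power was calculated for it. The text on recruitment outside Vermont names no western state. All of this stands.

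**Conclusion.** The point holds as a defect in how delivery is specified. Followed as written, with the natural reading of what a day is, the weekly window for Alaskan women in the incentives condition is about 1 to 9 a.m., against 5 a.m. to 1 p.m. in Vermont. That works against the protocol's own reason for the window. With equal allocation it concerns about 60 / 2 = 30 Alaskan women, plus any main-trial women in western time zones assigned to incentives. It rests on the assumed four-hour offset and on carrying the week-1 definition into the weekly phase.

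Three stronger readings are tempting and are not supported:
- **That Alaskan women would lose several hundred dollars.** That needs a miss rate, and a contrast with Vermont, where the same reading gives a 5 a.m. prompt. The protocol supplies neither. Only the cost of a single miss at the plateau, $60.25 to $86.25, can be derived.
- **That week 1 is impaired.** It is essentially unaffected.
- **That main-trial power or measured abstinence is wrong.** Neither is directly affected. Any influence on abstinence would come through weaker reinforcement.

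It should be corrected, because a feasibility arm is where a delivery artefact is most easily mistaken for a finding.

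**What to change.** In Treatment Conditions, define the day in each participant's own local time zone. In the weekly-phase text, state that the prompt and the eight-hour window run on that local clock. Set the app from the phone's time zone or the mailing address, and say in the same place whether the two-hour reminder applies in the weekly phase. The identical-procedures statements would then hold in practice as well as on paper. Leave the number and frequency of samples and the incentive values unchanged.

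The cost is a sentence or two of amendment and a time-zone setting in an app already being adapted to the study's specification. No extra samples, contacts or staff are needed.
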